### Study End Points and the Road Map for Their Evaluation

Students’ well-being will be assessed longitudinally by the 5-item World Health Organization Well-Being Index (WHO-5) at week 0, week 8, week 10, month 6, and month 12. The WHO-5 well-being index is a short global rating scale that measures subjective well-being for all populations, including adolescents. Positive well-being is another term for mental health (Figure 1) [33]. The key outcome measure includes the positive change in well-being, as estimated by the difference in postintervention (week 8 and week 10) and preintervention (week 0) WHO-5 mean scores by determining the *P* value and effect size using appropriate statistical tests. Although a difference in the mean WHO-5 score of >10 is considered clinically significant [33,34], a meta-analysis of meta-analyses concluded that universal prevention programs of this type in children have effect sizes between 0.07 and 0.16 [35]. Indeed, the difference in the mean WHO-5 score with an antidepressant (desvenlafaxine) vs placebo and wake therapy vs exercise was statistically significant but not clinically significant in patients with depression [36,37].

In children, the hope theory has been introduced on the concept that “goal-directed hopeful thinking” is a requisite for development and survival and is related to experiencing positive emotions [39-41]. Hope within students (≤16 years of age) will also be assessed longitudinally by age-appropriate hope scales at week 0, week 8, week 10, month 6, and month 12. Any improvement in “hope” will be estimated by the difference in postintervention (week 8 and week 10) and preintervention (week 0) mean scores by determining the *P* value and effect size using appropriate statistical tests. Hope theory is related to the theories of learned optimism, self-esteem, and self-efficacy, which are the key goals of the success4life program [42]. Students with “higher hope” have been found to attain higher academic achievement (at all levels of education) and higher graduation rates. They are also better problem-solvers and psychologically adjusted, can handle stress better, are healthier, and have higher self-esteem [43].

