### Ethics Considerations

At week 0, interested participants’ legal guardians will complete the “enrolment agreement form” as part of the onboarding process for parents and guardians. Informed consent will be obtained from the legal guardians of students. The program’s effectiveness will be assessed by a series of web-based questionnaires conducted on recruited students whose parents or guardians provided informed consent for the study. All the research questionnaires directed to the students are entirely anonymous, voluntary, and close-ended.

The research methodology is exempt from the requirement of ethics committee approval according to the Office for Human Research Protections, US Department of Health and Human Services, as the survey questionnaires will be completely deidentified [53,54]. Any suspected cases of justifiable concerns related to physical or mental health will be brought to the attention of relevant responsible party (eg, school counselors, parents, or legal guardians).

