Nonetheless, real-world studies on heterogeneous populations without randomization are subject to bias and confounders [71]. The scientific best practices roadmap we adopted for scientific strategies needed to draw valid causal conclusions on the effectiveness of the success4life program includes the adoption of robust and validated study end points and publishing of the study protocol to enhance study transparency. We also use neutral instead of negatively or positively phrased items and measures to avoid central tendency bias (in Likert scales) for the weekly workshop feedback questionnaires, using closed questions in the survey. We decided to make the response to all questions mandatory for submission of each feedback questionnaire to avoid any issues of missing values in data sets and to keep the surveys fully anonymous yet voluntary to prevent nonresponse bias [59,63,72,73].

Pessimistic explanatory style (self-talk and the way people explain to themselves why they experience bad or good events) leads to cognitive vulnerability to depression, poor health, and early mortality [74,75]. Many factors—for example, the explanatory style of parents (especially that of mothers) for their and their children’s events along with childhood trauma, chronic adversity, and abuse—influence the development of a pessimistic explanatory style as a trait [74-76]. Interventions aimed at changing a pessimistic explanatory style and outlook enhance mental and physical well-being and lower the likelihood of future illnesses [76,77]. This is also relevant for breaking the cycles of intergenerational trauma and ever-increasing psychological distress in the youth by promoting protective processes that not only buffer against life’s uncertainties but also intergenerational risk and provide immunization against mental health disorders [78,79].

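### Anonymous, voluntary surveys do not prevent nonresponse bias, and mandatory items cover only gaps within submitted forms, so selective nonresponse can shift the uncontrolled WHO-5 change

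*Protocol article*

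**What the plan says.** The Discussion lists measures meant to support valid causal conclusions. Two of them concern missing data. The first is: "We decided to make the response to all questions mandatory for submission of each feedback questionnaire to avoid any issues of missing values". The second is the decision "to keep the surveys fully anonymous yet voluntary to prevent nonresponse bias".

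The first is worded for feedback questionnaires and follows directly on a sentence about the forms completed after each weekly workshop. The second speaks of surveys in general, and Study End Points and the Road Map for Their Evaluation uses that same word for the WHO-5 and hope measurements at weeks 8 and 10. Ethics Considerations removes any doubt about scope: "All the research questionnaires directed to the students are entirely anonymous, voluntary, and close-ended". It also says that "the survey questionnaires will be completely deidentified".

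WHO-5 is measured "at week 0, week 8, week 10, month 6, and month 12". The key outcome is the "difference in postintervention (week 8 and week 10) and preintervention (week 0) WHO-5 mean scores". The Discussion rules out a separate control group. As yardsticks the article reports that "universal prevention programs of this type in children have effect sizes between 0.07 and 0.16" and that "a difference in the mean WHO-5 score of >10 is considered clinically significant".

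**The concern.** A mandatory-item rule works only on forms that are sent in. A student unwilling to answer one item can submit nothing, so a missing item becomes a missing questionnaire. Voluntary completion permits nonresponse. Anonymity may encourage students to answer, and to answer frankly, but it does not make those who answer representative of those who do not.

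This matters because of the design. If forms cannot be linked, the available contrast is between the mean of those who answered at week 0 and the mean of those who answered at week 8 or 10. A change in who answers then looks like a change in well-being. No control arm exists in which the same selection could be seen or offset. The Results section also makes phase 1 the external control for phase 2, so a distortion in phase 1 would carry into that comparison.

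**Working it through.** **No figure to reproduce.** The article states no dropout rate, SD, power or alpha, and says it has no statistical sample size calculation. The check therefore asks how much selection is needed, with no true change, to produce a shift as large as the article's own benchmarks.

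**Inputs from the article:** cited effect sizes 0.07 and 0.16 (read as SD units); clinical threshold above 10 WHO-5 points; no control group; no linking code mentioned.

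**Assumptions:** share of week 0 responders not answering later, d = 10–50%; SD = 20 points where points are needed; pre–post correlation 0.5 or 0.7 in the simulation.

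**Step 1: formula.** With unlinked waves and no true change, mean of later responders minus mean of all week 0 responders = d × g. Here g is the gap between responders and nonresponders in current well-being. The gap needed for a target shift is g = target / d.

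| d | g for 0.07 SD | g for 0.16 SD |
|---|---|---|
| 10% | 0.70 | 1.60 |
| 20% | 0.35 | 0.80 |
| 30% | 0.23 | 0.53 |
| 40% | 0.18 | 0.40 |
| 50% | 0.14 | 0.32 |

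**Step 2: in WHO-5 points.** The benchmark is 0.07 × 20 = 1.4 to 0.16 × 20 = 3.2 points. Three illustrative cases:
- 20% loss, gap 5 points: 0.2 × 5 = 1.0 point (0.05 SD), below the benchmark range.
- 30% loss, gap 8 points: 0.3 × 8 = 2.4 points (0.12 SD), inside it.
- 40% loss, gap 10 points: 0.4 × 10 = 4.0 points (0.20 SD), above it.

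**Step 3: the clinical threshold.** 10 / 20 = 0.5 SD. At 30% loss this needs g = 0.5 / 0.3, about 1.7 SD, which is not a credible gap.

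**Step 4: simulation.** Two million draws of bivariate normal scores with no true change, and logistic dropout with an odds ratio (OR) per SD lower current well-being. Linked means the change in students who answered both times.

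| Loss, OR | Unlinked shift (SD) | Linked, correlation 0.5 | Linked, correlation 0.7 |
|---|---|---|---|
| 20%, 1.5 | 0.08 | 0.04 | 0.02 |
| 30%, 1.5 | 0.12 | 0.06 | 0.04 |
| 40%, 1.5 | 0.16 | 0.08 | 0.05 |
| 30%, 2.0 | 0.19 | 0.10 | 0.06 |

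If dropout instead depends on baseline alone (30%, OR 2.0), the linked completers' change becomes −0.09 (correlation 0.5) or −0.06 (correlation 0.7). Linkage thus cuts the bias by half or more in the first setting and reverses its sign in the second. Linked completers alone are not a full remedy.

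**The case against.** The strongest reply is that the article is being read too broadly. The mandatory-item rule most naturally governs the post-workshop feedback forms, not the outcome scales. No analysis set is stated, the article refers to longitudinal assessment and change since baseline, and the handling of missing waves may sit in a full protocol or analysis plan that is not shown. The article also concedes, in general terms, that real-world data carry bias and confounding.

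Much of this stands. The mandatory-item half applies to the outcome waves at most by extension, and silence on missing-wave methods is no fault here. What does not yield is the positive statement that the survey design prevents nonresponse bias. It covers surveys generally, Ethics Considerations makes every student questionnaire voluntary, and no later analysis plan can make the statement true.

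A reader might infer four stronger things that the documents do not support:
- *That dropout would be invisible.* Forms per wave can be counted against roughly 100 recruits, and the learning management system tracks assignments and workshop completion (Intervention Course). What may be lost is who failed to respond and what they had scored before.
- *That selective dropout accounts for the whole expected effect.* The 0.07–0.16 range is cited for similar programs and not declared as this study's expectation. Reaching it depends on assumed dropout and selection.
- *That the bias must favour the program and grow to month 12.* Direction depends on who stops responding, and months 6 and 12 lie outside the key contrast.
- *That the plan sets everyone at week 0 against stayers later.* It says no such thing, and the week 0 survey is itself voluntary.

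**Conclusion.** The point holds as a correction to a stated assurance. The design does not prevent nonresponse bias, and mandatory items deal only with gaps inside submitted forms. With unlinked waves, 20–40% nonresponse and no true change, a modest gap (0.18–0.35 SD) gives a shift at the lower end of the cited range, and a moderate to large one (0.40–0.80 SD) gives the upper end. At 10% nonresponse the upper end would need a 1.6 SD gap and is implausible. A change above 10 points is not readily explained this way.

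These sizes rest on assumed dropout, gap, correlation and SD, and on the waves being unlinked, which follows from full anonymity and the absence of any mentioned code but is not stated outright. A small positive change of the size usual for such programs could therefore not be separated from selection, whereas a large one could not easily be dismissed on this ground.

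**What to change.** 1. Withdraw the statement that nonresponse bias is prevented, and limit the missing-values statement to item-level gaps in submitted forms.
2. Report the number enrolled and the number responding at each wave.
3. Before week 0, introduce a self-generated anonymous code so that one student's forms can be joined across waves. Check it first against the de-identification on which the ethics exemption rests. Linkage cannot be recovered afterwards.
4. Estimate within-student change with a model that uses all available waves, and do not difference means from different sets of responders.
5. Compare week 0 WHO-5 between students who later respond and those who do not.
6. Add one sensitivity analysis in which nonresponders show no gain or do worse. This is needed because the model in item 4 does not protect against dropout driven by unobserved current well-being.

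The cost is a small set-up step for the code and its check against the exemption, a response log, and some analysis text. The estimate may turn out less favourable.

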## Appendix

Multimedia Appendix 1 Broad overview of each workshop's specific details, including the theme, objectives, and specific IBL and PBL exercises. IBL: inquiry-based learning. PBL: project-based learning.

## Abbreviations

ABCDE: Adversity-Beliefs-Consequences-Disputation-Energization
CHS: Children’s Hope Scale
IBL: inquiry-based learning
LMS: learning management system
MSUD: mental and substance use disorder
PBL: project-based learning
PPI: positive psychology intervention
RCT: randomized controlled trial
RWD: real-world data
RWE: real-world evidence
SHS: State Hope Scale
WHO-5: 5-item World Health Organization Well-Being Index
